## Abstract

**Introduction::**

Psoriasis vulgaris (PV) is a chronic, painful, disfiguring, and disabling dermatological disease, which affects the physical and mental health of patients and impacts their quality of life. Current conventional systemic therapies can be costly, present risks of side effects, have limited efficacy and commonly recur following treatment cessation. Some Chinese herbal medicine therapies have shown therapeutic benefits for psoriasis vulgaris, including relieving symptoms and improving quality of life, and a potential of reducing relapse rate. However, explicit evidence has not yet been obtained.

**Methods and analysis::**

This is a pilot randomized controlled trial with the objective of investigating the effect of Jia Wei Liang Xue Xiao Feng San granules on relapse rate of recurrent PV and the correlation between Psoriasis area severity index (PASI) and key psoriasis-related cytokine changes and the number of cells. A total of 102 participants were recruited for this study, including 72 patients with recurrent PV, 15 healthy volunteers and 15 patients with psoriasis vulgaris who have recovered for more than 1 year. A total of 72 patients, with recurrent PV, will be randomized (1:1) to receive the oral Chinese herbal medicine Jia Wei Liang Xue Xiao Feng San or the oral Acitretin Capsule treatments for a period of 8 weeks. After this period, participants whose PASI scores improvement reached more than 75%, will undergo a 52-week follow-up phase.

The primary outcome measures are as follows:

The secondary study outcomes will include:

This trial may provide a novel regimen for recurrent PV patients if the granules decrease recurrence rate without further adverse effects.

**Ethics and dissemination::**

The ethics approval was provided by the Sichuan Traditional Chinese medicine regional ethics review committee. The ethics approval number is 2018KL-055. The design and the results of the study will be disseminated through peer-reviewed publications and conference presentations.

**Trial registration number::**

Chinese Clinical Trial Registry (ChiCTR1900022766).

## Introduction

1

Psoriasis is an immune-abnormal, chronic, proliferative skin disease,^[1]^ characterized by a well-defined and raised red patches (plaques) with adherent thick silvery scales. The cause of this disease is still not well known. This disease can involve the skin of the whole body that can be accompanied by nail and joint lesions, which relapse rates in the Chinese population result in a greater severity, affecting the physical and mental health of patients and impacting their quality of life. Due to the lack of clinically specific remedy, this disease has always been one of the most important diseases in the field of dermatology.^[2]^ The recurrence of psoriasis is a difficult problem for dermatologists and patients with psoriasis. Therefore, some scholars have purposed that the treatment is to control the development of psoriasis at an early stage to reduce the area involved, achieve and maintain long-term remission, and minimize side effects to improve patients’ quality of life.^[3]^

At present, routine therapies typically involve the application of local and systematic treatments. Few therapies were accepted by patients, especially systemic drugs. Although often effective, these are cautiously used, owing to concerns surrounding their safety profile, their long-term use and the frequent relapse after drug withdrawal. Chinese herbal medicine has been frequently used for symptoms associated with psoriasis. Clinical practices have proved that TCM is beneficial and effective in alleviating psoriasis clinical symptoms, improving quality of life, immune function, reducing metastasis and in preventing recurrence in various diseases.^[4]^ However, a rigorously designed, randomized and controlled trial to investigate how traditional Chinese Medicine can potentially reduce recurrence rate is required.

There are very few studies that investigated psoriasis mechanism of recurrence at home and elsewhere. The Carrascosa et al^[5]^ study found that the decrease in the number of CD4 cells was statistically significant with a persistent psoriasis remission. Casteljns et al^[6]^ confirmed that keratin 16 is significantly expressed in the asymptomatic skin, adjacent to a recurrent lesion, that Ki-67 expression increased at the edge of skin lesions and that keratin 14 is expressed in recurrent lesions at the initial recurrence stage of psoriasis. Flisiak et al^[7]^ confirmed that plasma IL- 18 concentration was associated with the severity of psoriasis and that the combined determination of plasma IL- 18 and TGF -β1 can be used as a possible sign of psoriasis activity. Friedrich et al^[8]^ also confirmed that the treatment with the immunoregulating IL-10 can reduce the recurrence rate and prolong the interval of psoriasis recurrence. We believe that the immune mechanism of psoriasis recurrence mainly focuses on the innate immune and acquired immune systems. A large number of basic studies have shown that psoriasis is an organ-specific inflammatory disease, where T cells dominate its pathogenesis and persist its inflammatory status.^[9]^

According to the traditional Chinese medicine theory and clinical observation, the Chinese medicine compound Jia Wei Liang Xue Xiao Feng San (JWXXF) was developed by a renowned Chinese herbal medicine clinician ([name]), and that the experimental results confirmed that^[10,11]^ JWXXF can have a positive effect in psoriasis treatment by inhibiting KC keratinization, preventing inflammation, inhibiting PCNA expression and regulating TNF-1. Therefore, a rigorously designed, randomized and controlled trial to investigate the possibility and degree of JWLXXF granules to reduce recurrence rate and to provide immunological basis for JWLXXF granules application in psoriasis recurrence treatment is required.

## Methods/design

2

This is a pilot randomized controlled trial for 3 years. In this study, a total of 102 participants will be enrolled, including 72 patients with recurrent PV, 15 healthy volunteers and 15 patients with psoriasis vulgaris who have recovered for more than 1 year. The entire trial consists of an initial assessment, a one-week screening phase (week 1), an 8-week observation phase (week 1 to week 8) and a 52-week follow-up phase (week 9 to week 60) (Fig. 1).

**Figure 1 F1:**
[figure not shown]
Test flow chart.

Potential participants will be invited to an initial assessment (first visit) consisting of an inclusion and exclusion criteria screening. If eligible, participants will be asked for informed consent and will undergo assessment of Psoriasis area severity index (PASI), dermatology life quality index (DQOLS), and score of Pruritus Degree by PGA, lesion photos and vital signs, full blood count, kidney and liver function blood tests, electrocardiogram, stool examination and urine (routine chemical examinations).

A total of 72 patients with recurrent PV will be randomized (in a 1:1 ratio) to receive oral Chinese herbal medicine JWLXXF or oral acitretin for 8 weeks. During the observation phase, psoriasis symptom measures will be self-reported by participants and recorded in a daily or weekly diary. Face-to-face assessments with blinded assessors will be scheduled at weeks 2, 4, 6, and 8 (Fifth visit), with further data collected, including assessment of PASI, DQOLS, and score of Pruritus degree by PGA, lesion photos, drug adherence, vital signs, adverse events and cause analysis of shedding (Table 1). The conversation will be made to 72 patients, at the time of medical treatment, to check adherence to the dosage guidelines and to monitor adverse events. Routine chemical examinations, laboratory assessments of efficacy and safety evaluation will also be scheduled at the end of the 8-week period.

**Table 1 T1:**
[figure not shown]
Evaluation measures and time points.

The 72 patients with recurrent PV, whose PASI scores improvement are more than 75%, will undergo a 52-week follow-up phase (week 9 to week 60), with further data collection, including assessment of PASI, routine chemical examinations, recurrence rate, remission period (This remission period - the last remission period) (Table 1).

For the 52-week follow-up phase, participants will continue to record symptoms in their daily or weekly diaries. At week 60, participants will attend an end of follow-up assessment (9th visit) which will mark the end of the trial.

## Setting and participants

3

There are 3 types of subjects in this study: 72 patients with recurrent PV, 15 healthy volunteers and 15 patients with psoriasis vulgaris, who have recovered for more than 1 year.

The recruitment will be performed through posters in local newspapers and hospitals and participants might also be invited to contact trial coordinators via their treating physicians (general practitioners, dermatologists, or immunologists). Research assistants will introduce and discuss the trial to potential subjects. They will be given a consent form and separate information sheets, including information on the main aspects of the trial. Patients will then be able to have an informed discussion with their family and participating consultants. The research assistants will obtain the signed consent from patients willing to participate in the trial.

### Eligibility criteria

3.1

#### Inclusion criteria

3.1.1

Patients will be included if they satisfy the following criteria:

(1)comply with the diagnostic criteria for psoriasis vulgaris as indicated in dermatovenerology 8th Edition;(2)comply with the diagnostic criteria for blood-heat syndrome as indicated in the Guidelines for the Clinical Research of Chinese Medicine New Drugs and New Dermatology of Traditional Chinese Medicine;(3)must be aged between 18 and 70 years;(4)An informed consent is provided; and(5)recurrent psoriasis patients must belong to the types of recurrence IV, V and VI^[12,13]^: Type IV (frequently limited type): The rash is extensive or limited at the first onset, and rashes occur every year afterward, but the amount of rash is small and is limited to certain parts of the body; Type V (frequently sparsely sparse): Psoriasis often recurs, with a wide range of rashes at the onset, but with a sparse density; Type VI (frequently issued): Psoriasis occurs every year, and the rash is widely distributed and numerous.

#### Exclusion criteria

3.1.2

People with any of the following will be excluded from participation:

(1)psoriasis with other skin diseases;(2)those with a known cancer, infection, electrolyte imbalance, acid-base disturbance or calcium metabolic disorder, known disorders of calcium metabolism (high blood calcium levels);(3)psychotic patients (self-assessment anxiety scale (SAS) scores > 50 or self-assessment depression scale scores > 53, or other psychiatric scores), hyperlipidemia, high vitamin A, pregnant and lactating, or plan to become pregnant within a year;(4)types of psoriatic arthritis or pustular psoriasis or erythroderma psoriaticum;(5)taking systemic drugs or phototherapy for psoriasis within the 4 weeks prior to screening and taking topical drug treatment for psoriasis within the 2 weeks prior to screening.

#### Elimination criteria

3.1.3

People with any of the following will be excluded from participation:

allergic to drugs used in the study;

cannot take medication and reviewers as required;

incomplete recording or automatic suspension of treatment;

during the experiment, the patient had a major negative event, such as illness or major mental stimulation.

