### Adverse events

3.7

(1)Ask and record the adverse events and degree of patients at each consultation after medication, and record, in details, the symptoms, occurrence, duration and disappearance times of adverse events.(2)The correlation between adverse events and drugs is assessed according to whether they are unrelated, possibly unrelated, possibly relevant, or relevant.(3)Incidence of adverse events = number of adverse events / total cases × 100%.(4)After treatment, the patients’ tolerance to drugs will be evaluated according to poor, moderate, light and high praise.

If adverse events occur or there were abnormal blood test results of liver and kidney function, the subjects will be advised to discontinue all drug treatments related to the test and seek medical advice from doctors for a safe continuation of the study.

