### Sample size calculation

3.8

Due to the unknown potential primary outcome at this stage, the sample size was calculated by reference to a standardized effect size. An effect size of 0.9 SD was chosen with consideration of the drug cost and patients’ motivation to adhere to the treatment. To detect a difference of 0.9 SD with 90% power using a 5% significance level, a sample size of 30 per arm would be required. Considering 20% dropout rate, the total sample size should be adjusted to 36 for each group.

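### Section 3.1.3 excludes randomised patients for events that arise on study, such as suspended treatment, incomplete records or illness, which can bias the comparison of the two arms

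*Protocol article*

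**What the plan says.** Section 3.1.3 (Elimination criteria) is separate from the pre-entry exclusions in 3.1.2 but has the same lead-in: "People with any of the following will be excluded from participation". Its four items are:

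1. "allergic to drugs used in the study"
2. "cannot take medication and reviewers as required"
3. "incomplete recording or automatic suspension of treatment"
4. "during the experiment, the patient had a major negative event, such as illness or major mental stimulation"

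Section 3.7 (Adverse events) says that if adverse events or abnormal liver or kidney tests occur, "the subjects will be advised to discontinue all drug treatments related to the test". The sentence closes by referring to going on safely with the study.

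Section 3.10 (Statistical analysis) compares the two groups and names no analysis population. Section 3.5.1 divides recurrences by the number of cases followed up. Sections 2 and 4.2 admit only patients who reach PASI75 at week 8 to the 52-week follow-up, and 4.2 ends a patient's follow-up at recurrence.

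**The concern.** Item 4 says in terms that it applies during the trial, and item 3 presupposes that treatment or recording has begun. These two items therefore act on patients who already have an allocation. The grounds are also unlikely to be independent of treatment and outcome:

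- **Suspension of treatment** may follow intolerance or lack of effect. Section 3.7 advises stopping the drug after an adverse event, which may lead straight to item 3.
- **Incomplete recording** is broad, because patients keep diaries through treatment and a year of follow-up (section 2).
- **Illness or mental stress** has no threshold, so applying it is a matter of judgement. It may also coincide with worsening or relapse.

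The regimens differ visibly (granules three times a day, acitretin once a day; section 3.2), so adherence and tolerability may differ by arm. Randomisation protects the comparison only while patients stay in it. PASI and recurrence are both primary outcomes, and the abstract rests the trial's value on less recurrence without added adverse effects, so this rule touches every part of the conclusion.

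**Working it through.** **Step 1: when each item can act.**

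| Item in 3.1.3 | Before randomisation | After randomisation |
|---|---|---|
| 1. Drug allergy | possible | possible |
| 2. Cannot comply with medication or reviews | possible, if read as a capability test | possible |
| 3. Incomplete recording or suspension | no | yes |
| 4. Major negative event | no | yes |

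**Step 2: which outcomes are exposed.** Items 1 to 3 can act in the 8 treatment weeks, so they affect week-8 PASI and PASI75 and decide who is left to enter follow-up. Incomplete recording and item 4 can also act in follow-up and so affect recurrence. Section 3.6 plans the week-8 safety tests in 72 patients, but someone no longer participating would not have them.

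**Step 3: the plan's own figures.** Section 3.8 states "An effect size of 0.9 SD was chosen", with 90% power, 5% significance, 30 per arm, and 36 after a 20% dropout allowance. Sidedness is not given; two-sided is assumed.

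- Normal approximation: n = 2 × (1.960 + 1.282)² / 0.9² = 25.9, so 26 per arm. The exact t-test gives 26.9, so 27. The stated 30 is not reproduced but is conservative.
- Dropout: 30 × 1.2 = 36, as stated. Dividing instead, 30 / 0.8 = 37.5, so 38.
- Expected loss: 0.20 × 72 = 14.4 patients.
- Power for 0.9 SD (t-test): about 96% with 36 per arm, and about 92% with 36 × 0.8 = 28.8 per arm.

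Power survives the planned loss, so the issue is bias.

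**Step 4: illustration of the bias.** Assumptions, none from the documents: the same true PASI75 rate p in both arms; a fraction r of an arm removed; everyone removed is a non-responder. The observed rate is then p / (1 − r). The rejection rate is for a two-sided 5% test of two proportions with 36(1 − r) patients per arm:

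Φ((d − 1.96·se0)/se1) + Φ((−d − 1.96·se0)/se1),

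where d is the observed difference, se0 the pooled and se1 the unpooled standard error.

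Example: p = 50%, removal 20% against 0%. Observed rates are 0.50/0.80 = 62.5% and 0.50/1.00 = 50.0%, so d = 12.5 points. With 28.8 and 36 patients, se0 = 0.124 and se1 = 0.123, and the rejection rate is 16.9%.

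| True PASI75, both arms | Removed, arm A / arm B | Observed A / B | False difference (points) | Rejection rate |
|---|---|---|---|---|
| 40% | 20% / 0% | 50.0% / 40.0% | 10.0 | 12.6% |
| 40% | 20% / 10% | 50.0% / 44.4% | 5.6 | 7.2% |
| 40% | 30% / 10% | 57.1% / 44.4% | 12.7 | 15.7% |
| 50% | 20% / 0% | 62.5% / 50.0% | 12.5 | 16.9% |
| 50% | 20% / 10% | 62.5% / 55.6% | 6.9 | 8.4% |
| 50% | 30% / 10% | 71.4% / 55.6% | 15.9 | 22.9% |
| 60% | 20% / 0% | 75.0% / 60.0% | 15.0 | 24.1% |
| 60% | 20% / 10% | 75.0% / 66.7% | 8.3 | 10.8% |
| 60% | 30% / 10% | 85.7% / 66.7% | 19.0 | 37.3% |
| any of these | 20% / 20% | equal | 0 | 5% |

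The heaviest unequal pattern, 30% / 10%, averages (30 + 10)/2 = 20% over the two arms, the same as the plan's dropout allowance.

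**The case against.** The strongest reply is that 3.1.3 speaks of participation, not of the data set. Analysis populations are commonly left to an analysis plan, which is not shown and could keep these patients. That stands as far as it goes: removal from the analysis is an inference. But the rule is stated, no other section qualifies it, and no later plan can recover outcomes that were not collected once a patient was out.

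Four stronger readings are tempting, and the documents do not support them:

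- **That all four items act after randomisation.** Allergy can be known at entry, and inability to comply can be a capability test. The list also sits under Eligibility criteria.
- **That adverse-event rates will be understated.** Section 3.7 records events at each consultation after medication and divides by total cases. Nothing says that events already recorded are dropped. Only later safety data are at risk.
- **That exclusions will differ by arm.** They may. With equal removal of the same pattern, the illustration shows no false difference.
- **That recurrence is distorted by a calculable amount.** With an assumed true rate of 60% in both arms, removing relapsers equal to 15% or 30% of one arm gives (0.60 − 0.15)/0.85 = 52.9% or (0.60 − 0.30)/0.70 = 42.9%, which is 7 or 17 points too low. But the 60% is invented, and only relapsers in one arm are removed. Recurrence is counted only among PASI75 responders and ends their follow-up, so a documented relapser has already reached the endpoint.

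The link from 3.7 to item 3 is also uncertain. The advice to stop the drug may envisage the patient staying in the study, and item 3 may mean stopping on the patient's own initiative. That is a reason to reconcile the two sections, not to assume either reading.

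**Conclusion.** The point holds in this limited form. Section 3.1.3 mixes possible entry criteria with at least two on-study events, and takes randomised patients out of participation for them. Those events may relate to treatment and outcome, so following the text can bias PASI, recurrence and safety.

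Neither the size nor the direction can be derived from the documents. The 6 to 19 points, with a false-positive rate of about 7% to 37% in place of 5%, apply to PASI75 only. They rest on assumed rates of 40% to 60%, unequal removal, and removal of non-responders only, which is an extreme pattern. They show that a material distortion is possible within the overall loss the plan allows for; they do not predict one.

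**What to change.** 1. Limit 3.1.3, as a ground for exclusion, to conditions known before randomisation.
2. State that meeting an on-study item does not remove a randomised patient from outcome collection or analysis, and continue the visits already scheduled for that patient.
3. Analyse week-8 PASI and PASI75 in all randomised patients in their assigned arm. Analyse recurrence in all PASI75 responders who enter follow-up, including those who later meet an item. Report safety in everyone who took at least one dose.
4. Use the present list only to define a secondary per-protocol set.
5. Reconcile the discontinuation advice in 3.7 with the suspension item in 3.1.3, so that it is clear whether a patient who stops the drug stays in the study. This needs no new rule on when treatment stops.

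The cost is a change of wording and keeping already planned visits for patients who would otherwise have left. There will be some missing data to handle, and the estimated effect will be slightly diluted. Because 60 patients had been recruited when the article was written (section 4.4), the change should also cover any already eliminated: keep the data collected from them and hold their remaining scheduled visits where possible.

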#### Inclusion criteria of healthy volunteers

3.1.4

Healthy volunteers’ inclusion criteria:

(1)aged between 18 and 65 years;(2)no family history of psoriasis;(3)people who did not use corticosteroids or immune agents within a month of the trial;(4)people without serious systemic diseases, tumors, immunodeficiency, or mental disorders.

### Interventions

3.2

The intervention group will receive individually packaged doses (n = 6 g) of JWLXXF, with each dose to be dissolved in warm water and orally consumed three times a day for 8 weeks. The control group will take 10 mg of Acitretin once every day for 8 weeks. The oral Chinese herbal medicine granule JWLXXF will be produced by the Department of Pharmacy, Sichuan Hospital of traditional Chinese Medicine, a manufacturer holding a Good Manufacturing Practice certificate. The Acitretin will be provided by the Chongqing Huabang Group, number H20010126.

### Concomitant treatment

3.3

According to the doctor's advice, white Vaseline can be used as a basic concomitant treatment to relieve dry skin and without taking other topical drugs during treatment.

### Randomization

3.4

Unpredictable randomized sequences were generated by computer and sealed in opaque and sequentially encoded envelopes. After determining the eligibility of the participants, the researchers will break the envelopes in order and assigned them to the appropriate test group. The person who will generate the random sequence will not be the same person as the assigned subject, and the random assignment will not be displayed until the end of the study.

### Outcome measures

3.5

#### Primary outcomes

3.5.1

(1)PASI: assess the severity of the disease.(2)Laboratory assessments: the number and distribution of Th1, Th2, Th17, Treg, Th22, and Th9 cells will be determined by ELISA. The expression of the transcription factors T-bet, GATA3, ROR gamma t, Foxp3 gene will be investigated by PCR and WB. The screening of cytokines, such as IFN-gamma, IL-4, IL-17A, IL-17F, IL-22, TGF-beta, IL-10 and IL-9 will be performed by Bio-Plex suspension chip.(3)Recurrence rate = recurrence cases/follow-up cases ∗100%

Note:

No recurrence criteria: the same as the end of treatment and lesion limitation. Recurrence criteria: new skin lesions appearing in the patients who were clinically cured or have the original skin lesions expanding, the color turning red, the scale increasing and the PASI score increasing for ≥ 1.

(1) Mitigation period: this remission period - the last remission period.

Note:

The last remission period: the time from the last clinical cure to the recurrence. This remission: the time interval from the end of JWLXXF treatment to the next recurrence.

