### Statistical analysis

3.10

SPSS Statistics 17.0 (IBM SPSS Inc., Armonk, NY) will be used for the statistical analysis of data, which will be carried out by independent statisticians. The Chi-square test will be used to evaluate the basic baseline characteristics and primary outcomes of the 2 groups. The Spearman rank correlation analysis of the correlation between PASI and biochemical indexes, will be used. The secondary outcomes will be evaluated by means, standard deviations and medians. The one way ANOVA test will be used to compare the mean of multiple samples, the LSD test for the homogeneous variance, and the Tamhane T2 test for the uneven variance. *P* < .05 will be considered as statistically significant.

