### Clinical efficacy evaluation basis

4.2

For moderate and severe psoriasis, PASI score is still the “gold standard” to evaluate the severity of psoriasis.^[29]^ According to the research, patients with sustained and efficient response to PASI score have a better quality of life score.^[30]^ According to the requirements of the new drug effective standard, after three months of test, the effective standard is a 75% improvement of the PASI score, which is called PASI75.^[29]^ PASI75 combined, with the pruritus score and DQOLS, can evaluate the short-term efficacy of JWLXXF. It needs a certain time to follow up on the recurrence rate and remission period to determine the long-term effect. After 8 weeks of treatment, patients with a pai75 will be followed up and this period will start from the end of the treatment. If there is no recurrence, the follow-up period is 1 year. If there is recurrence, the recurrence of the disease is the end point of the follow-up.

According to the guiding principles for clinical research on new drugs of traditional Chinese medicine (Part III), issued by the Ministry of health in 1997 and the directions of new drugs clinical research (try out) issued by the State Food and Drug Administration in 2002, the recurrence criteria are: new skin lesions appear in the patients who are cured clinically, or the original skin lesions expand, turn red, scale increase, and PASI score increase for ≥1. No recurrence criteria: the same as that at the end of treatment, but with limited skin lesions.^[31]^

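### The 90% power claim is for a difference in SD units, but the primary outcomes are to be tested by chi-square and short-term efficacy judged by PASI75; under the same shift that comparison has about 67–79% power

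*Protocol article*

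**What the plan says.** Four places in the protocol article bear on this.

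- **3.5.1 Primary outcomes** gives the first item as "PASI: assess the severity of the disease". It states no time point, change measure or responder threshold.
- **4.2 Clinical efficacy evaluation basis** says that "the effective standard is a 75% improvement of the PASI score, which is called PASI75", and then that "PASI75 combined, with the pruritus score and DQOLS, can evaluate the short-term efficacy of JWLXXF". The pruritus score and DQOLS are secondary outcomes in 3.6. The same 75% threshold also decides who enters the 52-week follow-up (section 2, Methods/design).
- **3.10 Statistical analysis** says: "The Chi-square test will be used to evaluate the basic baseline characteristics and primary outcomes of the 2 groups". It also plans Spearman correlations of PASI with the laboratory indexes, which use the score.
- **3.8 Sample size calculation** opens with "Due to the unknown potential primary outcome at this stage" and continues: "To detect a difference of 0.9 SD with 90% power using a 5% significance level, a sample size of 30 per arm would be required". A 20% dropout allowance brings this to 36 per arm.

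**The concern.** The analysis text and the sample size text assume different kinds of outcome. Chi-square and PASI75 fit a yes/no outcome, while a difference in SD units fits a continuous one. The two treat patients differently: someone who improves by 70% adds a large benefit to a comparison of scores and counts as a failure under PASI75. Cutting a score at a threshold discards information, so a sample size that suffices for the score generally falls short for the responder comparison.

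If PASI is analysed as 3.10 and 4.2 imply, the short-term comparison has a clearly higher chance of missing a true effect than 3.8 states. A null PASI75 result would then be read against a power figure that does not belong to it.

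**Working it through.** **Inputs from 3.8:** difference 0.9 SD, 5% significance (taken as two-sided, since sidedness is not stated), power 90%, 30 per arm, 20% dropout, 36 per arm. **Not in the article:** PASI75 rates in either arm. Control rates of 10% to 60% are assumed.

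**Step 1. The plan's own figure, as a comparison of means.**
n per arm = 2(1.960 + 1.282)² / 0.9² = 25.9, so 26. The t-test version gives 26.9, so 27. The stated 30 is somewhat larger than needed, which errs on the safe side.

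Power at 30 per arm: Φ(0.9 × √(30/2) − 1.960) = Φ(3.486 − 1.960) = 93.6%. With the noncentral t it is 92.9%. After 20% dropout, 36 × 0.8 = 28.8 remain per arm, and the t-test still has 91% to 92%. For a continuous outcome the 90% claim is met.

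**Step 2. The same shift as a responder comparison.**
Take improvement as normal with equal SD in both arms, and let a threshold give control response rate p_c. A shift of 0.9 SD then gives the other arm p_t = Φ(Φ⁻¹(p_c) + 0.9). For p_c = 30%: Φ(−0.524 + 0.9) = Φ(0.376) = 64.6%.

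Power of the uncorrected chi-square test with 30 per arm was found by enumerating all pairs of responder counts:

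| Control rate | Other arm | Power |
|---|---|---|
| 10% | 35.1% | 66.6% |
| 20% | 52.3% | 75.4% |
| 30% | 64.6% | 78.9% |
| 40% | 74.1% | 77.9% |
| 50% | 81.6% | 74.6% |
| 60% | 87.6% | 70.2% |

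The most favourable control rate, about 33%, gives 79%. Fisher's exact test would be lower, 55% to 71%.

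**Step 3. Could the planned numbers rescue it?**
With all 36 per arm evaluable, the chi-square power is about 75% to 84% over the same control rates. Reaching 90% would take 42 to 57 evaluable patients per arm (normal approximation for two proportions), against 30 planned.

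**Step 4. Type II error.**
For the score: 1 − 0.929 = about 7%. For responder status: 1 − 0.79 to 1 − 0.67 = about 21% to 33%.

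**The case against.** Several objections have force.

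- *The endpoints need not conflict.* A reader might infer that 3.5.1 defines a continuous primary endpoint which 4.2 then contradicts. The text does not go that far. Section 3.5.1 names an instrument, and PASI75 is derived from that instrument. Section 4.2 belongs to the Discussion and says only that PASI75 "can evaluate the short-term efficacy of JWLXXF". This stands. What survives is narrower: the stated test and the stated efficacy standard point to a yes/no result, while the sample size points to a mean.
- *The 0.9 SD was never tied to PASI.* This is correct. Section 3.8 says that the outcome was unknown. One therefore cannot say that the trial was sized on the PASI score, only that its power figure is for some continuous outcome and does not carry over to PASI75.
- *The choice of metric may be fixed elsewhere.* A reader might infer that the sponsor could pick the metric after seeing the data. The full protocol and analysis plan are not shown, so the article cannot establish this and the point does not rely on it.
- *The power range depends on a model.* It does. It compares a normal variable with its own dichotomy. A 0.9 SD difference in percent improvement is not shown to equal 0.9 SD in the baseline-adjusted week-8 score. Reading 0.9 as an arcsine effect size for proportions (for example 30% against 73.5%) would give about 94% power, but the text says SD and states no rates.
- *It is a pilot, and PASI is one of several primary outcomes.* Both are true, but the article still makes a formal 90% power claim and sets a 5% significance threshold.

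**Conclusion.** The point holds in limited form. The 90% power in 3.8 applies to a continuous outcome compared by means, and 30 per arm delivers it (93% by t-test). It does not transfer to the yes/no PASI comparison that 3.10 and 4.2 imply. There the same 0.9 SD shift gives about 67% to 79% power at 30 per arm, and less than 90% even if all 36 are evaluable.

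The shortfall appears at every control rate examined from 10% to 60%, but its exact size rests on the normal, equal-SD assumption, on two-sided testing and on response rates that the article does not give. The figures show how large the mismatch could be and are not an estimate of this trial's actual power. The matter should be corrected, but it does not undermine the trial's design as a whole.

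**What to change.** Make four wording changes.

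1. **3.5.1:** define the PASI primary outcome as the week-8 PASI score in all randomised patients.
2. **3.10:** for this outcome replace chi-square by a baseline-adjusted comparison of scores (ANCOVA), and keep chi-square for binary outcomes. Without this change, 3.10 would prescribe a test that does not suit the endpoint newly defined in 3.5.1.
3. **4.2:** name week-8 PASI75 as a supporting outcome. Its use for entry to follow-up stays unchanged.
4. **3.8:** state that the 0.9 SD / 90% figure applies to a continuous outcome such as the week-8 PASI score, and not to PASI75 or the recurrence rate.

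If the sponsor prefers PASI75 as the primary measure, the alternative is to keep chi-square and restate the power in 3.8 for two proportions, with the assumed response rates written down.

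The first route needs no extra patients or visits, because section 2 already schedules PASI at the first visit and at week 8. Its small downside is that PASI75, the more familiar figure, becomes supporting. The alternative also needs only wording, but the article would then have to state a lower power or a larger sample.
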